Despite not adhering exactly to the recommended model of CIT, these studies observed positive results such as an improvement in motor function, mobility, dynamic balance, discharge weight symmetry, gait ability, gait speed, length and width of step, and force of foot ground contact [26, 28]. However, in view of the above information, the investigation of the effects of the original LE-CIT protocol on gait functionality and balance of chronic hemiparetic patients following a stroke was not completely clarified.

The following research question was established to examine the effects of LE-CIT *vs* intensive conventional therapy on gait functionality and balance, as well as the transference of these gains in therapy to the environment outside the clinical setting in chronic hemiparetic patients following a stroke: is LE-CIT more effective compared with intensive conventional therapy with regard to gait functionality and balance in people suffering from stroke?

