### Sample size and justification

After a sample size calculation, realized through a pilot study with 10 randomized patients in each group, using G*Power3.1.9.2 Software, we employed a matched-pair t-test *a priori*, using mean and standard deviation of Mini-BESTest (with an effect size of 0.93—sample size of 12 for each group) and 6minWT (with an effect size of 0.65—sample size of 21 for each group) as the primary outcome. Considering for analysis an α 0.05 and β 0.80, 21 patients were estimated for each group, totalizing 42 patients for this study.

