#### Data analyses

The software Excel (Microsoft) will be used to tabulate the data and the software SPSS will be used to do the statistical analysis. A significance level of 5% will be adopted.

We will use the Kolmogorov-Smirnov test to analyze the normality of the data. For the characterization of the sample and baseline comparison to test the homogeneity of the sample, the Qui-Quadrado will be used, but if we find statistical differences between the groups we will also analyze the clinical relevance of these differences.

The results will be compared in relation to the type of intervention and at the three timepoints proposed in this study (pre-treatment, post-treatment, and at 6 month follow-up) using the two-way analyses of variance, ANOVA, and the Bonferroni post-hoc test or Friedman, depending on the parameterization of the data.

To analyze the direction and magnitude of outcomes, we will use the Pearson or Spearman test of correlation.

The results will be described with mean and standard deviation for each group and mean and standard deviation of differences between groups and confidence interval.

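### The sample size comes from a matched-pair t-test although the trial compares two independent arms, so the stated 80% power is not established for the between-group question

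*Protocol article*

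**What the plan says.** The protocol article (Methods, Sample size and justification) bases the calculation on "a pilot study with 10 randomized patients in each group" and says of the method: "we employed a matched-pair t-test". For Mini-BESTest it reports a calculation "with an effect size of 0.93—sample size of 12 for each group"; for the walk test it reports "6minWT (with an effect size of 0.65—sample size of 21 for each group". It concludes: "Considering for analysis an α 0.05 and β 0.80, 21 patients were estimated for each group, totalizing 42 patients for this study". The larger figure, from 6minWT, sets the trial's size. The pilot means and standard deviations are not given, and the effect sizes are not defined.

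The design is parallel. The Abstract has patients randomly allocated to LE-CIT or control, and the randomisation section reserves 21 places for each arm. The research question in the Background is between groups: "is LE-CIT more effective compared with intensive conventional therapy". Data analyses plans a two-way ANOVA on intervention and three time points, or Friedman, and says "A significance level of 5% will be adopted". Nowhere are patients matched across arms.

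**The concern.** A matched-pair test sizes a study in which each observation has a partner, and its answer is a number of pairs. Here that answer is used as the number of patients in each of two unrelated arms. For the same numerical effect size, a comparison of independent arms needs almost twice that number per arm, because the difference carries the sampling variation of both arms.

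The 6minWT is one of two primary outcomes and the one that fixed N. If its real power for the between-group question is well below 80%, a non-significant result says little, yet a reader who trusts the stated power could take it as evidence that LE-CIT is no better than intensive conventional therapy.

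**Working it through.** **Inputs.** From Sample size and justification: effect sizes 0.93 and 0.65, α 0.05, and the value labelled β 0.80, read as power 0.80. From the randomisation section: 21 per arm. Sidedness is not stated, so both versions were tried.

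**Formulas.** Exact noncentral-t power.
- Paired: df = n − 1, noncentrality = dz × √n, with n the number of pairs.
- Independent, equal arms: df = 2n − 2, noncentrality = d × √(n/2), with n per arm.

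**Step 1: reproduce the plan's figures.** Smallest n for 80% power at α 0.05:

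| Calculation | Effect 0.93 | Effect 0.65 |
|---|---|---|
| Paired, two-sided | 11.15, so 12 pairs | 20.58, so 21 pairs |
| Paired, one-sided | 9 pairs | 17 pairs |
| Independent, two-sided | 19.16, so 20 per arm | 38.14, so 39 per arm |
| Independent, one-sided | 16 per arm | 30 per arm |

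Of these four, only the two-sided paired test gives 12 and 21 (power 83.4% and 80.9%). The wording is therefore literal: numbers of pairs became numbers per group. The match also confirms that 0.80 is the power.

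**Step 2: power of the actual comparison, if 0.65 and 0.93 are between-group d.** With 21 per arm, df = 40.
- 6minWT: noncentrality = 0.65 × √(21/2) = 2.106; power 53.8%. Rounding of 0.65 moves this only between about 53% and 54%. Power of 80% would take 39 per arm, 78 in total.
- Mini-BESTest: noncentrality = 0.93 × √(21/2) = 3.014; power 83.7%.

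**Step 3: if they are paired effect sizes (dz).** Assuming equal SDs and a correlation ρ within pairs, d = dz × √(2(1 − ρ)). ρ is not in the document; the values below are assumptions.

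| Assumed ρ | 6minWT: d | Power, 21 per arm | Mini-BESTest: d | Power, 21 per arm |
|---|---|---|---|---|
| 0 | 0.92 | 83% | 1.32 | 99% |
| 0.3 | 0.77 | 68% | 1.10 | 94% |
| 0.5 | 0.65 | 54% | 0.93 | 84% |
| 0.7 | 0.50 | 36% | 0.72 | 62% |

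**Step 4: if they are within-arm pre-post changes.** Such an effect says how much one arm changed, not how far the arms differ. Between-group power cannot be derived from the document.

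**Step 5: a statement that needs no reading of 0.65 or 0.93.** Solving the independent two-sided formula for d at n = 21 and power 80% gives d = 0.886, about 0.89.

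**The case against.** The strongest reply is that 54% is not the trial's power. It assumes that 0.65 is a between-group d, which the article does not say, and a paired procedure takes dz. This stands. A reader might infer that the trial simply has 54% power on 6minWT, or that it needs 78 patients; the document supports either only under that reading. A reader might equally infer that Mini-BESTest is safe at 84%, but that rests on the same assumption and falls to about 62% if 0.93 is a dz with ρ 0.7. Nor does the article say what was paired, so it cannot be asserted that the calculation describes one group measured twice.

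A second reply is that the planned analysis uses repeated measurements, which can add power over a single two-sample test. This also stands in part. With baseline adjustment, and 0.65 taken as a between-group difference on the raw SD, power is d/√(1 − r²) put into the formula above: about 66% at an assumed baseline correlation r of 0.5, and 82% at 0.7. If 0.65 is instead on the change-score SD, it is about 61% at r 0.7. But the sample size section invokes no such correlation or model, so this gain does not justify the stated figure.

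Neither reply restores the calculation. It is also not a matter of detail left to a fuller document: the article states a specific test that contradicts its own design.

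**Conclusion.** The point holds. The arithmetic is right for the test named, but the test does not fit two independent randomised arms, and nothing elsewhere in the article repairs this. The stated 80% power is not established for the between-group comparison.

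The size of the shortfall is conditional on what the effect sizes are. As between-group d, 21 per arm gives about 54% for 6minWT and 84% for Mini-BESTest. As dz, 6minWT ranges from about 83% to 36% over assumed correlations of 0 to 0.7. As within-arm changes, it is unknown. All these figures assume a two-sided 5% test, 21 analysed per arm and, except where stated, no baseline adjustment. The β label is a slip with a plain meaning and adds nothing to the case.

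**What to change.** Rewrite the sample size paragraph, leaving N at 42:

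- Replace the paired calculation with one for two independent groups.
- State what 0.93 and 0.65 are. If they are not between-group standardised differences, recompute those from the two pilot arms.
- State that 21 per group gives 80% power only for d of about 0.89 or more (two-sided 5%, unadjusted two-sample comparison).
- Give 54% (6minWT) and 84% (Mini-BESTest) only if 0.65 and 0.93 are confirmed as between-group d. Writing them in unconfirmed would relabel values from a paired calculation.
- If power is claimed from a baseline-adjusted or repeated-measures analysis, name the model and the assumed correlation.
- Write power 0.80 in place of β 0.80.

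The cost is one paragraph, plus a short recalculation from the pilot data if the effect sizes prove not to be between-group. No patients are added. The drawback is that the stated power may become less favourable.

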### Randomization, blinding, and treatment allocation

#### Randomization procedure

Randomization will be realized through the allocation of vacancies (21 for each group) by a researcher who has no contact with the evaluation or intervention process. We created a spreadsheet with this sequence of allocation (intervention or control) and the distribution of the participants into the groups was made by sorting the order according to inclusion criteria and recruitment.

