**Self-reported measure**	
LE-MAL	T0, T1, T2

As primary outcomes we have chosen Mini-BESTest and 6min WT, one test for gait performance and one test for balance evaluation.

For the follow-up evaluations, patients will receive, at the end of the protocol, a date to return. Between 30 and 15 days before the date scheduled, we will call them to remember about that. In case of giving up from the protocol we will use all the data collected until the moment of renunciation (it has been predicted at the consent form).

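### For 6minWT, the stated 80% power holds only for one matched-pair t-test at unadjusted α 0.05, a test that the analysis section, with its Bonferroni post-hoc comparisons, does not list

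*Protocol article*

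**What the plan says.** The section on sample size and justification bases the calculation on a pilot study and names the test: "we employed a matched-pair t-test". It gives two results. The 6minWT entry reads "with an effect size of 0.65—sample size of 21 for each group"; for Mini-BESTest the effect size is 0.93 and the stated number 12 per group. The larger number is adopted: "Considering for analysis an α 0.05 and β 0.80, 21 patients were estimated for each group", which makes 42 in total. No adjustment for multiple comparisons enters this calculation.

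The Measurements section, below Table 1, confirms that both outcomes are primary: "As primary outcomes we have chosen Mini-BESTest and 6min WT". It names no primary time point. Both are measured at T0, T1 and T2.

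The Data analyses section adopts a 5% significance level and compares results by type of intervention and over the three time points, "using the two-way analyses of variance, ANOVA, and the Bonferroni post-hoc test or Friedman", the choice depending on the data. It does not say how many comparisons the Bonferroni step covers. It also promises between-group differences with a confidence interval. A matched-pair t-test is not among the listed analyses.

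**The concern.** The test that was powered and the tests that are planned are not the same, and they need not use the same significance level. A Bonferroni step over two or more comparisons judges each at less than 0.05, while the 80% was worked out at 0.05. The overall ANOVA tests do not say at which visit the arms differ, so a statement about T1 or T2 may well be read from the post-hoc step.

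This matters mainly for 6minWT, because it fixes the sample size and its calculation has almost no slack. If its decisive comparison is adjusted, a real walking benefit of the assumed size could be reported as not significant while the paper still states 80% power.

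**Working it through.** **Inputs.** All come from the sample size section: effect sizes d = 0.65 (6minWT) and d = 0.93 (Mini-BESTest), α = 0.05, and n = 21 per group. The figure printed as "Considering for analysis an α 0.05 and β 0.80" is read as power 0.80, the only reading that reproduces the stated sizes. Three time points come from the Data analyses section. The number of Bonferroni comparisons, k, is not given. It is therefore an assumption and is varied.

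**Formula, matched-pair test.** Two-sided power is P(|T′| > c). T′ is noncentral t with n − 1 degrees of freedom and noncentrality d√n, and c is the two-sided critical value of t at α/k.

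**Step 1: reproduce the plan's figures.**
- 6minWT: 0.65 × √21 = 2.979 and c = 2.086 on 20 df. Power is 80.9%, and 21 is the smallest n that reaches 80%.
- Mini-BESTest: 0.93 × √12 = 3.222 and c = 2.201 on 11 df. Power is 83.4%, and 12 is the smallest n.

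Both stated sizes reproduce exactly. The alternatives do not: one-sided paired tests give 17 and 9, and two-sided independent-groups tests give 39 and 20 per group.

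**Step 2: same method, n = 21, with α divided by k.**

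| k | α per comparison | 6minWT power | n for 80%, 6minWT | Mini-BESTest power |
|---|---|---|---|---|
| 1 | 0.05 | 80.9% | 21 | 98.2% |
| 2 | 0.025 | 70.8% | 26 | 95.9% |
| 3 | 0.0167 | 64.4% | 28 | 94.0% |
| 6 | 0.0083 | 53.3% | 33 | 89.3% |
| 9 | 0.0056 | 46.9% | 35 | 85.8% |
| 15 | 0.0033 | 39.3% | 39 | 80.6% |

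Here k = 3 is the number of pairs among T0, T1 and T2, and k = 15 is every pair of cells in a 2 × 3 layout (6 × 5 / 2). For k = 3 the 6minWT line is c = 2.613 against the unchanged noncentrality of 2.979.

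The unadjusted margin for 6minWT is 80.9 − 80 = 0.9 points, so any family of two or more takes it below 80%. Mini-BESTest stays above 80% across the whole range.

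**Step 3: which contrast these figures describe.** A matched-pair test compares a patient with himself or herself, for example T0 with T1. The research question is between arms. The protocol does not say whether 0.65 and 0.93 are within-patient or between-arm effect sizes. If they are between-arm, the calculation uses 2n − 2 = 40 df and noncentrality d√(n/2). For 6minWT that is 0.65 × √10.5 = 2.106.

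| α | 6minWT, independent groups, n = 21 | Mini-BESTest, independent groups, n = 21 |
|---|---|---|
| 0.05 | 53.8% | 83.7% |
| 0.0167 | 35.8% | 69.5% |

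The 64.4% in Step 2 is therefore valid only for a within-patient contrast. The same limit applies to the 94.0% for Mini-BESTest.

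**The case against.** The strongest reply is that the protocol does not fix the adjusted level. With two arms there is only one between-arm comparison at a given visit, and Bonferroni over arms leaves it at 0.05. The figure of three comes from pairs of time points, which is not the between-arm question. This stands: on that reading Bonferroni costs nothing.

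Second, the protocol does not say that the post-hoc tests carry the decision. The ANOVA comes first at 5%, Friedman is the alternative, and the 80% is stated for the t-test, not for every follow-up comparison. Sizing on one contrast and then adjusting post-hoc tests is common practice and not in itself a contradiction. The exact make-up of the family may be set in an analysis plan that is not shown. This also stands as a limit on the claim. It does not remove the mismatch, because the test that was powered is not listed in the analysis section, and no power is given for the analyses that are listed.

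A reader might go further and infer that 21 per group simply fails to give 80% at the level the post-hoc tests use. The documents do not support that. They state no family size, and Mini-BESTest holds 80.6% even at k = 15 on the paired basis. The 65.7% for Mini-BESTest at n = 12 and α 0.0167 does not bear on the trial, because 21 per group are planned. Nor is there an arithmetic error: both stated sizes reproduce.

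Finally, it can be said that using a paired test to size a comparison of two independent groups is the larger problem. If 0.65 is a between-arm effect size, that is so: it costs more power (80.9% to 53.8%) than a family of three does (80.9% to 64.4%). It is a separate matter, but any restated power has to take account of it.

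**Conclusion.** The point holds in a limited form. For 6minWT, which sets the sample size, the 80% is true of one matched-pair t-test at unadjusted α 0.05 and of nothing else the protocol describes. If the decisive 6minWT contrast lies inside a Bonferroni family of two or more, its power on the plan's own basis is below 80%: 70.8% for two comparisons, 64.4% for the three time-point pairs, and lower for larger families. If it stands alone at 0.05, the Bonferroni step takes nothing away.

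This rests on three things: a two-sided test, which the reproduction supports; an assumed family size, hence a range and not a single figure; and the paired calculation taken literally. Mini-BESTest is not affected in the same way on that basis. What the protocol needs is a match between the power statement and a named test. The figures do not by themselves show that the trial is too small.

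**What to change.** Make the sample size and Data analyses sections refer to the same test at the same level. Either of two wordings would do:

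- **(a)** Name one between-arm contrast (outcome and time point) for each primary outcome. Test it at α 0.05 outside the Bonferroni family, apply Bonferroni only to the remaining pairwise comparisons, and limit the power statement to the named contrasts.
- **(b)** Keep the contrast inside the Bonferroni family, state how many comparisons the family holds, and restate the 6minWT power for 21 per group at that adjusted level.

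Under both, say whether 0.65 and 0.93 are within-patient or between-arm effect sizes, and compute the restated power for the test that will carry the conclusion. Copying 64% into the protocol would be right only for a within-patient contrast in a family of three. Keeping 80% under (a) would be wrong if 0.65 is a between-arm effect size, since the figure is then about 54%.

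The cost is wording in two sections and a short recalculation, with no extra patients or visits. The drawback is that the stated power for 6minWT becomes less favourable under (b), and under (a) as well if the effect size is between-arm.

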### Randomization, blinding, and treatment allocation

#### Randomization procedure

Randomization will be realized through the allocation of vacancies (21 for each group) by a researcher who has no contact with the evaluation or intervention process. We created a spreadsheet with this sequence of allocation (intervention or control) and the distribution of the participants into the groups was made by sorting the order according to inclusion criteria and recruitment.

#### Blinding

To minimize evaluation bias, the evaluators responsible for screening and outcome evaluations will be blinded for the group that the patient belongs to. Moreover, the physiotherapist responsible for applying the protocols will not have contact with the test outcomes, but she will be aware of which group the patients belong to. Patients will not be informed to which group they will be allocated. They will probably be able to identify the treatment received, once it is written on the informed consent, but during the protocol they will be asked not to tell the evaluator which kind of treatment they have been submitted to.

#### Training of therapists and treatment of participants

The main evaluator is an experienced physiotherapist, trained for each chosen test and unaware of the patient’s group allocation. The physiotherapist responsible for applying the protocol (first author) has 10 years of experience with neurological patients; she has also received CIT training (for upper and lower extremities) in a total workload of 64 h and was trained by the creators of LE-CIT. She has been involved in clarifying and adjusting the protocol, making decisions and discussing specific cases.

#### Intervention group (LE-CIT)

The participants in this group will be submitted to physiotherapy 3 h/day for 15 consecutive days. The physiotherapy will be divided into 2 parts: the first 30 min will be dedicated to the transference package and 2.5 h of intensive training. The CIT protocol is composed of [16]:
Shaping—method based on principles of behavioral training in which the motor or behavioral aim is approached in small steps by successive approximation, which means that the task may be hampered by the patient’s motoric capacities or may stimulate the patient to perform the same activity faster. Every functional task is performed 10 times and feedback is given on each attempt. This activity is chosen from the shaping bank considering (a) specific articular movement where the main deficit lies, (b) the joint movement that is believed to have potential for improvement, and (c) preference for associating tasks that have a similar potential to produce specific improvements. Each shaping program is individualized and has 8–12 tasks selected from the shaping bank. However, new tasks may be created for each participant to improve their motor deficits. For instance, to improve weight-bearing on the paretic side you can ask the patient to move the non-affected limb to touch “X”s placed on the floor in front of their feet, to the side, and forward while standing. The therapist can record how many cycles the patient can complete over 30 or 45 s. When it gets easier (i.e., the quantity of completed cycles increases), the therapist can place the “X” a bit further away, or increase the balance demand (by reducing the base of support, or replacing the stable surface for an instable one such as a foam).*Behavioral strategies of adherence (transference package):* These are strategies used to improve adherence through *Monitoring, Problem solving, and Behavioral contract.*○ *Monitoring:* This involves strategies which lead the patient to observe and document their performance (activity mode, duration, frequency, effort perception, and physiological answer to the activity) through LE-MAL and home diary.○ *LE/MAL and home diary:* In the daily administration of LE/MAL the patient answers questions about the participation of the impaired limb in daily activities, the period of reference being “from the last time that I asked you”.○ *Problem solving:* The LE-MAL and home diary checking provides an opportunity to discuss which barriers were encountered when using the impaired limb in real life situations and to use this information to then find solutions (environmental and task adaptation). It has to be done every day during the protocol.○ *Behavioral contract*: This is a formal agreement between the therapist, patient, and caregiver made on the first day. At this moment, the patient is committed to using their impaired limb during specific daily activities.○ *Homework*: Patients choose 10 activities on the second day that they are going to try to perform at home: 5 that they believe will be easy to achieve and 5 that they believe will be more challenging. This list must be completed in about 30 min and will be revised during the first 30 min on the next day, every day during the protocol. For each activity, they must check if it was done or not, if they do not perform their task they must write (in the comments space) the reason for not completing the task. They are requested to conduct all the tasks listed; however, they are informed that they must complete at least 70% of the list. It is worth emphasizing that the homework list is part of the behavioral package which means transference of learned movements during therapy to daily life (within functional tasks).○ *Schedule*: In this schedule the patient writes down the time spent on each activity in the list and how long they rested for.
